# **Protocol NKEBN/8/2010 (last amendment 01.05.2012):**

**Acronym Title:** TregVac

**Clinical Phase:** Phase 1 [classified by the Ethics Committee] **Accrual Objective: 20 [**10 subjects in Tregs arm and 10 subjects in control arm]

**Accrual Period: 12** months **Follow-up Period: 24** months

**Study duration: 36** months

**Place:** Medical University of Gdańsk, Department of Immunology and Department of Pediatrics, Hematology and Oncology; National Blood Bank, Gdańsk Unit

**Study Design:** A prospective, non-randomised pilot study to investigate the safety and efficacy of cellular therapy of recent-onset type 1 diabetes (DM1) with ex vivo expanded CD4+CD25+CD127- T regulatory cells.

**Treatment Description:** Patients will receive a single or double infusions of ex vivo expanded autologous CD4+CD25+CD127- T regulatory cells (Tregs) in a total dose of up to 30x106cells/kg b.w. All the patients will be on standard insulin therapy. (amended 01.05.2012)

**Primary Endpoint:** Success of the treatment will be defined as a proportion of patients with higher C-peptide and lower requirement for exogenous insulin in the treated group in comparison with the control individuals. The key endpoint is:

- The proportion of subjects with no reported adverse effects of the treatment from day 0 to two years after administration of Tregs. The day of Tregs infusion is designated Day 0 (as recommended by the Ethics Committee).
- The proportion of subjects with daily insulin dose (DDI) ≤ 0.5UI/kg b.w. and plasma fasting C-peptide levels more than 0.5ng/mL present without any stimulation at Day 365. The day of Tregs infusion is designated Day 0.

**Secondary Endpoints:** The key secondary endpoints are the following:

1. The proportion of subjects with daily insulin dose (DDI) ≤ 0.5UI/kg b.w. and plasma fasting C-peptide levels >0.5ng/mL present without any stimulation at 120days after the administration of Tregs. The day of Tregs infusion is designated Day 0.
2. The proportion of subjects with daily insulin dose (DDI) ≤ 0.5UI/kg b.w. and plasma fasting C-peptide levels >0.5ng/mL present without any stimulation from Day 0 to two years after the administration of Tregs. The day of Tregs infusion is designated Day 0.
3. The proportion of subjects with ≥15% reduction of DDI/kg b.w. from baseline at 120days after the administration of Tregs. The day of Tregs infusion is designated Day 0.
4. The proportion of subjects with ≥15% reduction of DDI/kg b.w. from baseline at 2 years after the administration of Tregs. The day of Tregs infusion is designated Day 0.
5. The proportion of subjects with ≥2% reduction of HbA1c from baseline at 120days after the administration of Tregs. The day of Tregs infusion is designated Day 0.
6. The proportion of subjects with HbAlc ≤6.5% at 120days after the administration of Tregs. The day of Tregs infusion is designated Day 0.
7. The proportion of subjects with HbAlc ≤7.0% at 120days after the administration of Tregs. The day of Tregs infusion is designated Day 0.
8. The proportion of subjects with HbAlc ≤6.5% at Day 365. The day of Tregs infusion is designated Day 0.
9. The proportion of subjects with HbAlc ≤7.0% at Day 365. The day of Tregs infusion is designated Day 0.
10. The proportion of subjects with HbAlc ≤6.5% from Day 0 to two years after the administration of Tregs. The day of Tregs infusion is designated Day 0.
11. The proportion of subjects with HbAlc ≤7.0% from Day 0 to two years after the administration of Tregs. The day of Tregs infusion is designated Day 0.

Efficacy Endpoints:

At 120 ± 14 days following the adoptive transfer of Tregs:

- - - - - The proportion of subjects with DDI ≤ 0.5UI/kg b.w.
        - The proportion of insulin-independent subjects
        - C-peptide levels
        - HbAlc levels
        - Quality of life (QOL) measures
        - Functional tests results [can only be performed when indicated by medical conditions of the patients and NOT solely as an efficacy check as recommended by the Ethics Committee]

At 365 ± 14 days following the adoptive transfer of Tregs:

- - - - - The proportion of subjects with DDI ≤ 0.5UI/kg b.w.
        - The proportion of insulin-independent subjects
        - C-peptide levels
        - HbAlc levels
        - Quality of life (QOL) measures
        - Functional tests results [can only be performed when indicated by medical conditions of the patients and NOT solely as an efficacy check as recommended by the Ethics Committee]

At 2 years ± 14 days following the adoptive transfer of Tregs:

- - - - - The proportion of subjects with DDI ≤ 0.5UI/kg b.w.
        - The proportion of insulin-independent subjects
        - C-peptide levels
        - HbAlc levels
        - Quality of life (QOL) measures
        - Functional tests results [can only be performed when indicated by medical conditions of the patients and NOT solely as an efficacy check as recommended by the Ethics Committee]

Safety End Points:

Day of the Treg infusion:

- Assessment of the incidence and severity of immediate Adverse Effects resulted from the administration of Tregs (reactions of the hypersensitivity, embolism) and blood drawing (>2 g/dL decrease in haemoglobin concentration)

14 days following the adoptive transfer of Tregs:

- Assessment of the incidence and severity of possible Adverse Effects resulted from the infusion of Tregs including: viral, bacterial, or fungal infections, and benign or malignant neoplasms,

120 ± 14 days following the adoptive transfer of Tregs:

- Assessment of the incidence and severity of possible Adverse Effects related to the infusion of Tregs including: viral, bacterial, or fungal infections; and benign or malignant neoplasms.

365 ± 14 days following the adoptive transfer of Tregs:

- The incidence and severity of possible Adverse Effects related to the infusion of Tregs including: viral, bacterial, or fungal infections; and benign or malignant neoplasms,

2 years ± 14 days following adoptive transfer of Tregs:

- The incidence and severity of possible Adverse Effects related to the infusion of Tregs including: viral, bacterial, or fungal infections; and benign or malignant neoplasms,

Cessation of the Trial Criteria:

- Any severe Adverse Effect in two or more patients with confirmed link to the administration of Tregs

Inclusion Criteria:

Patients who meet all of the following criteria are eligible for participation in the study:

TREGS STUDY ARM

1. Male and female patients 5 to 18 years of age.
2. Ability to provide written informed consent by parents (and patients if above 16years old)
3. Clinical history of autoimmune type 1 diabetes diagnosed within recent 2 months and presence of at least one type of anti-islet autoantibody: antiGAD, antiIA2, IAA, ICA (high titer),.
4. Fasting plasma C-peptide more than 0.4ng/mL
5. Involvement of the patients and parents in the intensive diabetes management defined as self monitoring of glucose values no less than three times/ day and by the administration of insulin injections each day or insulin pump therapy.
6. Patient and parents mentally stable and able to comply with the procedures of the study protocol.
7. Appropriate venous access for blood drawing.

CONTROL GROUP ARM :

1. Patients fulfilling the inclusion criteria from 1 to 6 but
2. EXCLUDED from blood drawing due to inappropriate venous access.

Exclusion Criteria:

Patients who meet any of these criteria are not eligible for participation in the study:

1. No agreement for participation in the study and no inform consent singed
2. Other than autoimmune type 1 diabetes
3. Age below 5 and above 18 years at the time of recruitment
4. Carriage of HLA-DQB1*0602 allele
5. IgA deficiency or other genetic defect present
6. Body mass index (BMI) outside the range of 25-75 percentiles for a particular age.
7. Presence or history of active infection including hepatitis B, hepatitis C, HIV, syphilis or tuberculosis (TB). Subjects with laboratory evidence of active infection are excluded even in the absence of clinical evidence of active infection.
8. Invasive aspergillus, histoplasmosis, or coccidioidomycosis infection within one year prior to study enrollment.
9. Any history of malignancy
10. Baseline Hb below the lower limits of the reference range ; lymphopenia (<l,000/uL), neutropenia (<l,500/uL), or thrombocytopenia (platelets <100,000/uL).
11. Known hypercoagulative state.
12. Medical treatment requiring chronic use of drugs other than insulin
13. Treatment with any anti-diabetic medication other than insulin within 4 weeks of enrolment (special attention to exclude anti-CD3 treated patients).
14. Diabetic retinopathy.
15. Arterial hypertension.
16. Presence or history of macroalbuminuria (>300 mg/g creatinine).
17. For female subjects older than 15 years positive pregnancy test, unwillingness to use effective contraceptive measures for the duration of the study and 4 months after discontinuation, when appropriate. For male subjects: intent to procreate during the duration of the study or within 4 months after discontinuation or unwillingness to use effective measures of contraception when appropriate.
18. Excessive anxiety of the patient or parents related to the procedures.
19. Any medical condition that, in the opinion of the investigator, will interfere with safe participation in the trial.
20. For parents and children older than 15 years: known active alcohol or substance abuse.

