Patients’ identity will remain confidential throughout the study period unless disclosure is required by law. It has been included in the Informed Consent Form that the data may be shared by study personnel other than the Primary Investigator, representatives of the approved government agencies, the Ethics Committee, and other regulatory agencies. Patients will be identified only by a unique identifier number. All data records and computers containing information about subjects specifically relevant to this study will be maintained in a locked, secured office. All study results for studies performed by hospital laboratories for which the results are posted on the Hospital computer system will be maintained by a secured password system with all the confidentiality safeguards afforded to patients receiving routine, non-experimental care. The results of this study may be published and presented in scientific meetings, however, the patient will not be identified in such publications or presentations.

- 1. **Adverse effects**

Definition of adverse event: any unfavorable and unintended sign (including an abnormal laboratory finding), symptom, or disease temporally associated with the use of a medical treatment or procedure regardless of whether the sign, symptom or disease is considered related to the medical treatment or procedure.

Definition of serious adverse event (SAE): any event that is fatal or life-threatening, that is permanently disabling, requires or extends hospitalization of the subject, represents a significant overdose or breach of protocol, or suggests that a drug or procedure used in a research protocol has produced congenital anomaly or cancer, or, in the opinion of the investigator, represents other significant hazards or potentially serious harm to the research subject or others.

Severity grading scale:

Mild: adverse event of little clinical significance

Moderate: adverse event of mild to severe significance; causing some limitation of usual activities

Severe: see definition of SAE above

Attribution scale:

Not related: clearly not related to the study

Possible: may be related to the study

Probable: likely related to the study

Definite: clearly related to the study

Unable to assess

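### The first key endpoint scores any versus no treatment-related adverse effect, sets no attribution cut-off or control comparison, and is a weak measure of an excess of common infections

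*Protocol*

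**What the plan says.** The opening summary of the protocol, under Primary Endpoint, lists as its first key endpoint "The proportion of subjects with no reported adverse effects of the treatment from day 0 to two years after administration of Tregs". It then fixes the time origin: "The day of Tregs infusion is designated Day 0 (as recommended by the Ethics Committee". The study is "A prospective, non-randomised pilot study" with "10 subjects in Tregs arm and 10 subjects in control arm" and 24 months of follow-up. The introductory sentence of Primary Endpoint compares treated with control children, but on C-peptide and insulin requirement. The safety line itself names no comparison, no severity threshold and no attribution level.

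Other places bear on what counts:

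- Safety End Points, 120-day entry: "Assessment of the incidence and severity of possible Adverse Effects related to the infusion of Tregs including: viral, bacterial, or fungal infections". Benign and malignant neoplasms are listed as well, and similar entries stand at 14 days, 365 days and 2 years.
- Section D, Adverse effects: an adverse event is "any unfavorable and unintended sign (including an abnormal laboratory finding), symptom, or disease temporally associated with the use of a medical treatment or procedure", whether or not it is thought to be related. The attribution scale there has five levels: not related, "Possible: may be related to the study", probable, definite, and unable to assess.
- Cessation of the Trial Criteria: a severe effect counts only if its link to the Tregs is confirmed.

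Section B.5 (Follow up of the patients) gives treated children a schedule of study visits. For controls it specifies only that blood is taken at routine visits.

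**The concern.** The same set of events can give quite different values of this endpoint, depending on how the two uncertain attribution levels are counted. The protocol does not settle this, and its own passages do not share one standard. Attribution is also an unblinded judgement: the study is non-randomised, and Section 3.5.1 makes the principal investigator, together with the Ethics Committee, the safety monitor.

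The form of the endpoint adds a second weakness. If Tregs raised the frequency of ordinary infections, no single infection would identify itself as caused by the cells. The signal would be more infections per child than in comparable children. If such infections are not attributed, the endpoint misses them. If they are counted as possible, a child fails at the first one and later ones add nothing. At stake is whether the first key endpoint of a Phase 1 study in children can inform about one of the harms that the protocol itself lists.

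**Working it through.** The protocol states no expected event rate, target proportion or power for this endpoint, so there is no figure of its own to reproduce.

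**1. Which events count.** The words 'of the treatment' exclude events rated not related. Probable and definite events are naturally included. Possible and unable to assess are left open. The Safety End Points speak of possible adverse effects and include infections, which points to a wide count. The cessation criterion requires a confirmed link, which points to a narrow one.

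**2. If infections count: event-free proportion and power.**

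Inputs from the protocol: 10 children per arm, 2 years. Assumed: infection rate r per child-year in controls, doubled under Tregs, with independent children. The mean count m over two years is 2r in controls and 4r in treated children.

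- Poisson: P(event-free) = exp(−m).
- Between-child variation (gamma, shape 2): P(event-free) = (1 + m/2)^(−2).

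Example at r = 1, controls: exp(−2) = 0.135; (1 + 1)^(−2) = 0.25. Treated: exp(−4) = 0.018; (1 + 2)^(−2) = 0.111.

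Power for proportions comes from full enumeration of a one-sided 5% Fisher exact test, 10 versus 10. Power for counts comes from simulation of a one-sided 5% Welch test on square-root counts per child. Its simulated size was about 4% to 5%.

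| Rate r per child-year | Event-free controls, Poisson | Power, proportion | Power, counts | Event-free controls, gamma shape 2 | Power, proportion | Power, counts |
|---|---|---|---|---|---|---|
| 0.5 | 37% | 18% | 51% | 44% | 12% | 34% |
| 1 | 14% | 3% | 77% | 25% | 8% | 43% |
| 2 | 1.8% | 0% | 97% | 11% | 1% | 51% |
| 4 | 0.03% | 0% | 100% | 4% | 0% | 57% |

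At r = 0.25 the proportion does less badly but still trails: 17% against 33% (Poisson) and 12% against 25% (gamma shape 2). With stronger variation (gamma shape 1), count power at the four tabulated rates falls to about 26%, 31%, 34% and 36%. The proportion has 10%, 8%, 4% and 1%.

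The reason is structural. With no treated child event-free, Fisher's test needs at least 4 event-free controls: p = C(10,4)/C(20,4) = 210/4845 = 0.043, whereas 3 give C(10,3)/C(20,3) = 120/1140 = 0.105. When few controls are event-free, no result in the treated arm can show an excess.

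A different pair of tests, both two-sided at 5% (Fisher, and an exact conditional test on Poisson counts), gives the same pattern at r = 0.5, 1 and 2: 8%, 0.5% and 0% against 37%, 70% and 95%.

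**3. If only clearly attributed events count.** Section A reports that none of the 8 patients in the earlier Treg trial had side effects, so 10 of 10 event-free is a likely result here. The one-sided 95% upper limit for the true risk would then be 1 − 0.05^(1/10) = 26%. With a true attributable risk of 20%, at least one event in 10 children has probability 1 − 0.8^10 = 89%. With 5% it is 1 − 0.95^10 = 40%.

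**The case against.** The case on the other side is substantial.

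- **The endpoint is not all-cause.** It counts effects of the treatment, and Section D has a not-related category. A reader might infer from the all-cause definition in Section D that nearly every child must fail. That definition is of an adverse event, and the endpoint's wording is narrower. What stays open is the handling of possible and unable to assess.
- **Values near 0% or near 100% are not document figures.** They depend on assumed rates. At 0.25 to 0.5 infections per child-year the Poisson event-free proportion is 61% to 37%, and with gamma shape 2 it is still 25%, 11% and 4% at 1, 2 and 4 per year. The floor is softer than a pure Poisson model suggests.
- **Incidence and severity are collected elsewhere.** The Safety End Points assess both at several times, and Section D provides for team review of descriptive adverse event statistics. It would be wrong to say that the trial as a whole treats a cold and a malignancy alike.
- **The endpoint can show some harm.** To say that it cannot show whether Tregs cause harm goes too far: frequent, clearly attributable harm would probably be seen (89% at a 20% risk).
- **No comparison was promised.** This is a Phase 1 pilot with 10 infused children, and low power for a doubled infection rate contradicts nothing in it.

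The last point explains why the power figures serve only to compare two summaries of the same data. None of the objections supplies the missing attribution rule, or gives an unattributed excess of infections a comparison with controls. The existing incidence endpoints make the repair easier, but they set no such comparison.

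**Conclusion.** The first key endpoint is incompletely fixed, because its value depends on an attribution cut-off that the protocol leaves open. It is also a weak measure of one particular harm, an excess of common infections. Counts per child do better than the event-free proportion at every rate tried, and also when between-child variation is applied to both. Under gamma shape 2 the gap runs from 12% against 34% at 0.5 per year to 0% against 57% at 4 per year.

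The size rests on assumed infection rates, a true doubling, equal recording of infections in both arms and otherwise comparable children. The direction did not change under any assumption tried. The documents do not support the stronger conclusions that the endpoint is uninformative about all harm or should be abandoned. This should be corrected, but it does not invalidate the safety assessment.

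**What to change.** 1. Keep the endpoint and state in its definition which attribution levels count, settling possible and unable to assess explicitly. Report it with an exact confidence interval, so that 10 of 10 event-free is read together with the 26% one-sided upper limit.
2. Alongside it, analyse infections regardless of attribution as the number per patient-year in each arm. Give the Treg-to-control rate ratio with an interval that allows for between-child variation, for example from a negative binomial model.
3. Define Day 0 for controls, who have no infusion: for example, recruitment plus the typical time from recruitment to infusion. Take the same infection history at comparable intervals in both arms. Without this, the closer follow-up of treated children could bias the rate ratio.
4. Report serious adverse events and neoplasms separately by arm.

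Replacing the endpoint with a composite of infusion reactions, neoplasms and serious adverse events of any attribution is not recommended. The Section D definition of a serious event includes breaches of protocol, and such a composite would drop the haemoglobin fall after blood drawing that the Safety End Points name.

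The cost is an amendment to one endpoint, a small extra analysis and an infection history from controls at routine visits. The comparison remains non-randomised, with controls chosen for inadequate venous access, and 10 per arm is imprecise. It should be presented as an estimate with its interval, not as a test of safety.

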**Follow-up visit schedule**

|  | **R1** | **A2** | **0d3** | **+14d** | **+2m** | **+4m** | **+6m** | **+9m** | **+1y** | **+15m** | **+18m** | **+21m** | **+24m** |
| --- | --- | --- | --- | --- | --- | --- | --- | --- | --- | --- | --- | --- | --- |
| Clinical examination | x | X | x | x | x | x | x | x | x | X | X | x | x |
| Insulin requirement | x | X | x | x | x | x | x | x | x | X | X | x | x |
| HbA1c (%) | x | X | x | x | x | x | x | x | x | X | X | x | x |
| C-peptide | x | X | x | x | x | x | x | x | x | X | X | x | x |
| Quality of life | x |  | x |  | x |  | x |  | x |  | X |  | x |
| Treg phenotype | x |  | X | x | x | x | x | x | x | X | X | x | x |
| Autoantibodies | x |  | X | x | x | x | x | x | x | X | X | x | x |
| Cytokines | x |  | X | x | x | x | x | x | x | X | X | x | x |

1 – recruitment

2 – Blood drawing

3 – Tregs infusion

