**5.1.4 Quality of life**

Generic and disease-specific measures adapted from other studies will be used to assess quality of life.

Generic Measures

Version 2 of the SF-36® Health Survey, standard (4-week) recall form.

This widely used, generic instrument derives eight scales (physical functioning, role-physical, bodily pain, general health, vitality, social functioning, role-emotional, mental health) and two summary components (physical and mental). If the 36-item version of the instrument were felt to be too lengthy, version 2 of the SF-12 (standard recall form) would be an option. This shorter version would derive eight scales and two summary components and would be also be normed to the 1998 data (general population and disease-specific groups).

Disease-targeted Measures

Diabetes Distress Scale

The Diabetes Distress Scale (DDS) represents the latest iteration of the Problem Areas in Diabetes (PAID) scale. This is a 17-item self-administered questionnaire culled from a longer battery of 28 items. Psychometric properties for the DDS were previously published in Diabetes Care. The DDS measures four diabetes-related distress domains: emotional-burden (EB), physician-related interpersonal distress (PD), regimen-related distress (RD), and diabetes-related interpersonal distress (ID). Internal consistency as measured by Cronbach's coefficient alpha ranged between 0.88 and 0.93 for the multi-item scales. The developers tested for and demonstrated construct validity using exploratory factor analysis.

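### Quality of life is listed as a 120-day efficacy endpoint, but the visit schedule does not collect it at +4 months, the only visit in that window

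*Protocol*

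**What the plan says.** In the protocol synopsis, the Efficacy Endpoints are grouped under three time points: 120 days, 365 days and 2 years after the infusion, each with a tolerance of 14 days. The first group is headed "At 120 ± 14 days following the adoptive transfer of Tregs". All three groups contain the item "Quality of life (QOL) measures".

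The Follow-up visit schedule has 13 columns: R (recruitment), A (blood drawing), 0d, +14d, +2m, +4m, +6m, +9m, +1y, +15m, +18m, +21m and +24m. Its quality-of-life row reads "Quality of life | x | | x | | x | | x | | x | | X | | x". For comparison, the C-peptide row reads "C-peptide | x | X | x | x | x | x | x | x | x | X | X | x | x", marked at every visit.

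Section 5.1.4 names two instruments. The generic one is the SF-36 version 2 with a 4-week recall, and a shorter form is left open: "If the 36-item version of the instrument were felt to be too lengthy, version 2 of the SF-12" would be an option. The disease-specific one is the Diabetes Distress Scale: "This is a 17-item self-administered questionnaire culled from a longer battery of 28 items". The first inclusion criterion is "Male and female patients 5 to 18 years of age".

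**The concern.** An endpoint list and a visit schedule have to agree, because sites work from the schedule. Here the list asks for a measurement at a time when the schedule does not take it. If nothing is changed, the 120-day quality-of-life endpoint will be empty, or will be filled from a visit well outside the protocol's own tolerance.

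Day 120 is not a marginal time point in this protocol. Five of the eleven numbered key secondary endpoints (numbers 1, 3, 5, 6 and 7) are set at 120 days. Quality of life could not be read alongside insulin dose, C-peptide and HbA1c at that time, although the efficacy list puts them together.

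**Working it through.** The plan gives no figure to reproduce here. The check sets the endpoint windows against the schedule.

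**Inputs**
- Endpoint times and tolerance: 120, 365 and 730 days (2 years), each ± 14 days (synopsis, Efficacy Endpoints).
- Visits and the quality-of-life row: Follow-up visit schedule.
- Assumption: the schedule is in months, so I convert at both 30 and 30.44 days per month.

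**Step 1: read the row.** The row has 13 cells for 13 columns, so no cell has been lost. Quality of life is marked at R, 0d, +2m, +6m, +1y, +18m and +24m (7 visits) and blank at A, +14d, +4m, +9m, +15m and +21m (6 visits). The marks alternate regularly. The other seven rows (clinical examination, insulin requirement, HbA1c, C-peptide, Treg phenotype, autoantibodies, cytokines) are all marked at +4m, so the blank there is specific to quality of life.

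**Step 2: find the visit in each window.**

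| Endpoint | Window (days) | Visit in window | Day of visit | Quality of life marked? |
|---|---|---|---|---|
| 120 days | 106 to 134 | +4m | 120 to 122 | No |
| 365 days | 351 to 379 | +1y | 360 to 365 | Yes |
| 2 years | 716 to 744 | +24m | 720 to 731 | Yes |

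No other visit falls in any of the three windows under either conversion.

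**Step 3: distance of the nearest quality-of-life visits from day 120.**
- +2m: 2 × 30.44 = day 61; 120 − 61 = 59 days early; 59 / 14 = 4.2 times the tolerance.
- +6m: 6 × 30.44 = day 183; 183 − 120 = 63 days late; 63 / 14 = 4.5 times the tolerance.
- Gap to the edge of the window, taking the more favourable conversion each time: 106 − 61 = 45 days and 180 − 134 = 46 days.

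**Step 4: could the recall period bridge the gap?** The SF-36 form named has a 4-week (28-day) recall. Completed at day 61 it covers about days 33 to 61, and at day 183 about days 155 to 183. Neither period overlaps days 106 to 134.

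Under the schedule as written, therefore, no patient has a 120-day quality-of-life value, and no neighbouring visit can reasonably stand in for it.

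**The case against.** The strongest case on the other side concerns importance. Quality of life is not a primary endpoint and is not among the eleven numbered key secondary endpoints. It is one of six items on the efficacy list, and only one of its three time points is affected. The trial is a non-randomised phase 1 pilot with 10 subjects per arm, and no sample size or stopping rule depends on this measure. All of that stands, and it limits the weight of the point. It does not remove the contradiction between the list and the schedule.

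Section 5.1.4 invites several stronger readings, which the protocol does not support.

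- *A change of instrument during the trial.* A reader might infer that patients can be switched from SF-36 to SF-12 part-way, spoiling within-patient change. The text says only that the shorter form would be an option if the longer one were felt to be too long. The natural reading is a choice left open at set-up. The same section gives both forms eight scales and two summary components, and no change-from-baseline endpoint is defined for quality of life.
- *Young children cannot complete the forms.* The protocol describes only the Diabetes Distress Scale as self-administered. It does not say who completes the SF-36 or SF-12. It gives no age limit for any of the forms, and it calls the measures adapted from other studies, which leaves room for adaptation.
- *Bias that differs between arms.* A reader might suppose that controls, chosen for poor venous access, are younger and so answer differently. No ages by arm are given, and controls must meet the same age criterion.

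What remains of the instrument question is narrower. For an age range starting at 5, no child or proxy form and no respondent is named, and the choice between SF-36 and SF-12 is open. That calls for clarification and is not a demonstrated error.

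**Conclusion.** The contradiction is exact: the 120-day quality-of-life endpoint cannot be measured under the schedule, because the one visit in its window does not collect it and the nearest assessments miss day 120 by about 59 and 63 days. The conclusion rests only on the endpoint list, the intact table row and the conversion of months to days, and either conversion gives the same answer.

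The impact is minor. A reader might infer that quality of life as a whole is lost, but the 365-day and 2-year endpoints both have a matching visit. The primary endpoint and the numbered secondary endpoints are untouched.

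**What to change.** Mark quality of life at the +4 month visit in the Follow-up visit schedule and keep the +2 month assessment. The visit already takes place, so the cost is one table cell and one more questionnaire session per patient. Moving the assessment from +2 to +4 months is less attractive, because it gives up the earliest assessment after the day of infusion for no need.

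If a 120-day quality-of-life reading is not wanted, delete the item from the 120-day efficacy list. That reconciles the two places equally well and costs nothing in data collection, but it gives up the endpoint.

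As a separate clarification, section 5.1.4 should state before enrolment which form is used (SF-36 or SF-12), which version applies at the younger ages, and who answers for each child, with the same form and respondent at every visit. The cost is some work on choosing the forms, with no extra visit.
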